#### Statistical Methods

Patients’ characteristics will be described at D1 and M6 using the mean and SD for quantitative data, frequency, and percentage for qualitative data.

The primary outcome to assess the feasibility of the study will be the proportion of patients achieving the physical activity recommendations corresponding to 150 minutes per week of moderate physical activity evaluated by the IPAQ score during the last week of the study. In addition, we will estimate the proportion of patients who agreed to participate in the ABLE Trial among eligible patients. The reasons for refusal will be documented and described as well.

The secondary outcomes to assess will be the evolution of physical activity, anthropometric, physical fitness, psychological, and biological variables between the initiation (D1) and the completion (M6) of the physical activity intervention using Wilcoxon signed-rank tests. In addition, the level of physical activity according to biological, psychological, and clinical outcomes adjusted on potential confounders, including age, treatment, and number of visits, will be explored using multiple linear regressions. Moreover, the level of oxidative stress will be correlated to the RECIST criteria. Data on barriers and facilitators of the adherence to a physical activity program from D1 to M6 will be compared by Mac Nemar tests. All statistical analyses will be performed using SAS software (version 9.4. SAS Institute Inc, Cary, NC, USA).

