**Figure 1 figure1:**
[figure not shown]
Participant flow chart for the Advanced stage Breast cancer Lifestyle and Exercise study, Lyon, France (PA: Physical activity).

Patients are encouraged to accumulate at least 150 minutes per week of moderate-to-vigorous intensity physical activity to maintain and improve health benefits. In addition, patients are asked to walk at least 30 minutes per day, increase their activities in their daily routine, and reduce their sedentary time. Several individual strategies are established with patients to attain their objectives (eg, using stairs whenever possible and walking for groceries or shopping). Moreover, meetings at the center with physical activity instructors are proposed depending on patients’ needs. Patients receive feedback at least monthly from their instructor. For patients undergoing chemotherapy, meetings take place during their day care visits at the cancer center. For patients with hormonal therapy treatment, meetings occur by phone or during a consultation with a physician in the center.

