The International Physical Activity Questionnaire (IPAQ) [41] is used to measure the self-reported physical activity. IPAQ (long form) is a validated self-administered physical activity questionnaire with 31 items and covers 4 activity domains, work-related physical activity, transportation physical activity, domestic physical activity, and recreational physical activity [41]. IPAQ gives specific scores in the metabolic equivalent of task (MET)-minutes/week for walking, moderate-intensity, and vigorous-intensity activity within each of the work, transportation, domestic chores and gardening (yard), and leisure-time domains. Questions are coded and converted in MET per minute and per week according to the Compendium of Physical Activities [42] by multiplying the number of METs by the duration and frequency of the activity. Then, the total physical activity score for each intensity is obtained by adding the score for this intensity in each domain and by adding the number of MET-minutes per week at each intensity.

**Table 1 table1:** The data collection schedule for the Advanced stage Breast cancer Lifestyle and Exercise Trial.

Assessments		Time		
		Patients’ recruitment	Day 1: Baseline	Month 6: End of the study

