**Other**				
	Reason for refusal	✓		

^a^Height, weight, waist-to-hip circumference, and body mass index.

^b^During 6 months.

Next, the global score of physical activity is divided into 3 categories commonly used by physical activity guidelines (<600 MET-minutes/week is equivalent to low physical activity; between 600 and 3000 MET-minutes/week is equivalent to moderate physical activity; and >3000 corresponds to high physical activity [43]). Furthermore, the sedentary time in minutes per week is obtained by adding the weekday sitting time in minutes for 5 weekdays, and the weekend sitting time in minutes for 2 days.

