## Discussion

### Principal Findings

Given the beneficial effects of physical activity in localized breast cancer, the ABLE Trial is the first European study to propose a physical activity intervention for patients with metastatic cancer that will obtain preliminary data on biological, functional, psychological, and clinical outcomes and identify the determinants of physical activity. In addition, the use of wearable activity trackers in the ABLE Trial strengthens its novelty. Although wearable activity trackers are comparable to pedometers in some aspects, they are more effective for behavioral modification [52] because the Health Mate app and the wearable activity tracker provide more detailed data on the physical activity performed over time. These types of devices are emerging in the health care field and are being shown to help motivate people to increase their physical activity level and facilitate them to reach a personal or recommended goal because of the feedback received in real time (eg, steps) [23-25]. International recommendations for patients with cancer are to practice 30 minutes of moderate physical activity per day at least 5 times a week [53]. The number of steps per day is more easily comprehensible for individuals to achieve these physical activity recommendations. For adults with health impairment, 5000-7000 steps per day might be a more appropriate target than the target of 10,000 steps per day recommended for healthy people [54]. Indeed, walking is feasible at no charge and practiced by the majority of people. In the ABLE Trial, the recommended number of steps is individualized to each patient because research has suggested that a small goal is more effective and easier to achieve than a higher activity goal. In addition, it is important to increase these physical activity targets gradually [24].

The links between the level of physical activity and the biological mechanisms involved in the tumor progression have never been studied in patients with metastatic breast cancer. A study of the oxidative stress in this population might help identify potential new biomarkers associated with physical activity and tumor progression.

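### The primary outcome is worded as moderate activity on the IPAQ while the prescribed target is moderate-to-vigorous, so a patient who meets the target partly or wholly through vigorous activity can be counted as a failure

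*Protocol article*

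**What the plan says.** Under Intervention (Adapted Physical Activity Program), the target is stated in terms of both intensities: "Patients are encouraged to accumulate at least 150 minutes per week of moderate-to-vigorous intensity physical activity". The Abstract gives the same target. A further request follows in the Intervention text: "patients are asked to walk at least 30 minutes per day".

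Statistical Methods defines the primary feasibility outcome as the proportion of patients who reach the recommendations, taken as "150 minutes per week of moderate physical activity evaluated by the IPAQ score during the last week of the study". Vigorous activity and walking are not mentioned there, and no particular IPAQ score is named.

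The section Physical Activity Fitness and Sedentary Behavior describes the instrument. It yields scores in MET-minutes per week "for walking, moderate-intensity, and vigorous-intensity activity within each of the work, transportation, domestic chores and gardening (yard), and leisure-time domains". Scores are summed over domains within each intensity, and a total is then formed "by adding the number of MET-minutes per week at each intensity". After Table 1, the global score is cut into categories, the lowest being "<600 MET-minutes/week is equivalent to low physical activity".

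The Discussion (Principal Findings) cites the international recommendation as "30 minutes of moderate physical activity per day at least 5 times a week", which appears to be where the endpoint's wording comes from.

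**The concern.** The target and the primary outcome name different intensity classes, and the instrument that links them keeps those classes apart. Moderate is one of the IPAQ's own scored classes, so a programmer could reasonably take the outcome to mean the moderate score alone. That rule fails patients who did what they were asked. The other rule that the article supports, the global score cut at 600, can classify the same patient the opposite way, and it can also pass a patient who has no moderate or vigorous minutes.

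The proportion is the trial's stated primary result, and the article says that the results will help design a multicenter randomized trial. If it is unclear what counts as success, the feasibility percentage cannot be interpreted or compared with that of a later trial.

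**Working it through.** The article gives no expected proportion or success threshold for the primary outcome, so there is no planned figure to reproduce. Two figures in it do link up:

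- Recommendation: 30 min × 5 = 150 min/week.
- Category cut: 600 MET-min ÷ 150 min = 4 METs, so 600 MET-minutes equals 150 minutes at 4 METs.

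**Inputs from the article:** at least 150 min/week moderate-to-vigorous; walking at least 30 min/day, i.e. 30 × 7 = 210 min/week; cut-off of 600 MET-min/week.

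**Assumed:** MET weights, which the article does not print. Two sets are used for walking/moderate/vigorous: 3.3/4/8 and 2.5/3/6.

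**Rules compared:** moderate minutes ≥150; moderate + vigorous minutes ≥150; global score = (walking weight × walking min) + (moderate weight × moderate min) + (vigorous weight × vigorous min) ≥600.

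| Weekly minutes | Moderate only | Moderate + vigorous | Global, 3.3/4/8 | Global, 2.5/3/6 |
|---|---|---|---|---|
| A: 150 moderate, 210 walking | 150, success | 150, success | 693 + 600 = 1293, success | 525 + 450 = 975, success |
| B: 75 moderate, 75 vigorous, 210 walking | 75, **failure** | 150, success | 693 + 300 + 600 = 1593, success | 525 + 225 + 450 = 1200, success |
| C: 150 vigorous, 210 walking | 0, **failure** | 150, success | 693 + 1200 = 1893, success | 525 + 900 = 1425, success |
| D: 210 recorded as walking only | 0, failure | 0, failure | 693, success | 525, failure |

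**B and C** meet both time requests in the Intervention section, yet fail the literal rule. That result uses minutes only. Without the walking they would still pass the global score: B scores 300 + 600 = 900 or 225 + 450 = 675, and C scores 1200 or 900.

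**D** shows the opposite risk. She passes the global rule whenever walking is weighted at 600 ÷ 210 = 2.86 METs or more, without one recorded moderate or vigorous minute.

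**Domains.** Work and domestic activity enter the global score. As the article describes the scoring, they also enter the moderate score, which is summed over domains too. Counting them is therefore not peculiar to one reading, but the definition should say so.

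**Possible size.** The article gives no data on how much activity is vigorous. As an illustration only, take n = 60 and an assumed true adherence of 60% (36/60; exact 95% CI 46.5% to 72.4%). Misclassifying a share of the adherent patients gives:

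- 10%: 36 × 0.9 = 32.4, about 32/60 = 53%
- 20%: 36 × 0.8 = 28.8, about 29/60 = 48%
- 30%: 36 × 0.7 = 25.2, about 25/60 = 42%

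**The case against.** The best defense is that the literal reading was never meant. The outcome is framed as reaching the recommendations, with the 150 moderate minutes given as what they correspond to. This can be read as an equivalent dose. It follows the Discussion's wording of the guideline, and the 600 MET-minute cut equals 150 minutes at 4 METs. On that reading vigorous activity counts and B and C pass. Minutes can also be recovered, since the score is built from duration and frequency, and exact scoring is often left to an analysis plan. Finally, this is a single-arm feasibility study with a descriptive proportion and no formal sample-size calculation.

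Much of this stands. The global reading is plausible, and MET units are no obstacle. But Statistical Methods does not adopt the 600 cut; the article uses it only to label activity categories. Nor is this just omitted detail, because the stated intensity class differs from the prescribed one.

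Three stronger inferences are tempting, and the article does not support them:

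- *A patient who only does the daily walk is fully adherent and wrongly failed.* Walking is requested in addition to the 150-minute target. She meets that target only if her walking is at least moderate in intensity, and her result on the 600 rule depends on an assumed MET weight.
- *The rule was chosen after the data were seen.* Analysis began in February 2018, after follow-up ended, but an analysis plan that is not shown may have fixed the rule.
- *Housework and job activity should be excluded from the primary outcome.* The intervention itself encourages more activity in the daily routine, so that exclusion would create a new mismatch.

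**Conclusion.** The point holds in this form: the primary outcome, read as written, does not match the prescribed target and is not tied to one IPAQ computation. At patient level the effect is complete reversal. B and C meet the target, fail the moderate-only rule, and pass both the moderate-plus-vigorous rule and the global rule under either set of assumed weights. The failure under the literal rule rests on no assumption beyond the article's statement that the IPAQ scores the intensities separately.

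The effect on the reported percentage is unknown. The fall from 60% to between 53% and 42% depends on an assumed adherence and assumed misclassification shares, and would be small if few patients do vigorous activity. Because this is the stated primary outcome and the items needed are already collected, the definition should be settled before the result is reported.

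**What to change.** Reconcile the Intervention section and Statistical Methods with one explicit definition, for example:

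*Primary responder: at least 150 minutes of moderate plus vigorous activity in the last week of the study, computed from IPAQ days × minutes and summed over all domains.* The definition should also state whether IPAQ walking minutes count.

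Named sensitivity analyses:

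- (a) walking + moderate + vigorous minutes ≥150. This captures moderate-intensity walking recorded under the walking items. It belongs here because the requested 210 minutes of walking would pass it alone at any pace, making the moderate-to-vigorous target redundant.
- (b) global score ≥600 MET-min/week, with the MET weights stated.
- (c) optionally, a version restricted to the leisure and transport domains.

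Since analysis began in February 2018, give the date of the clarification and report the literal moderate-only proportion as well, so that readers can see what the choice changes. If an existing analysis plan already fixes the rule, cite it and its date.

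Cost: a reworded endpoint and a few extra lines of code, with no new data. The primary percentage may come out lower than under the 600 MET-minute rule.

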**Objective:**

The primary objective of this study is to assess the feasibility of a 6-month physical activity intervention with activity trackers in patients with metastatic breast cancer (the Advanced stage Breast cancer and Lifestyle Exercise, ABLE Trial). Secondary objectives are to examine the effects of physical activity on physical, psychological, anthropometrics, clinical, and biological parameters.

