### Study Population

The inclusion criteria for this study are as follows: (1) female; (2) aged 18-78 years; (3) newly diagnosed with primary or secondary metastatic breast cancer histologically confirmed (ie, within the last 3 months) and treated in a cancer center by chemotherapy or radiotherapy or hormonal therapy or targeted therapy; (4) Eastern Cooperative Oncology Group Performance status <2; (5) able to speak and understand French and able to complete questionnaires and follow instructions in French; and (6) valid health insurance affiliation. For patients willing to participate in the study, confirmation from their treating oncologist of no contraindications to physical activity is required.

The exclusion criteria for this study are as follows: untreated brain metastases; pregnancy; and contraindications to physical activity (eg, uncontrolled hypertension, cardiac disease). All patients must sign an informed consent form.

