### Data Collection

Table 1 provides the complete data collection schedule in this study.

All assessments are recorded at the baseline and the end of the 6-month physical activity program (M6) by the instructor, as seen in Figure 1.

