#### Biological Data

A 7-mL blood sample is collected at the baseline (D1) and at the end of the study after 6 months (M6). The sample is centrifuged within half an hour after drawing and kept at 4°C before and during centrifugation. The plasma is distributed into cryotube aliquots of 1 mL and buffy coat in a single 1-mL cryotube; these cryotubes are frozen and stored at −80°C at the center and used for the analyses of oxidative stress and antioxidant biomarkers. Superoxide dismutase, catalase, glutathione peroxidase enzymatic activities, and markers of DNA oxidation (8-hydroxy-2'-deoxyguanosine), prostaglandins oxidation (8-Iso Prostaglandin F_2α__)_ are measured in the plasma [50]. Furthermore, levels of circulating growth factors, cytokines, neutrophils, monocytes, and natural killer cells are assessed as previously described [51].

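### The confounders named for the exploratory activity–outcome regressions leave out the D1 activity and D1 outcome values the trial collects, so stable health differences between women can appear as an activity association

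*Protocol article*

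**What the plan says.** The relevant text is in the protocol article under Statistical Methods. The secondary analysis relates "the level of physical activity according to biological, psychological, and clinical outcomes adjusted on potential confounders, including age, treatment, and number of visits", and this "will be explored using multiple linear regressions". The sentence does not say at which visit the level is taken.

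D1 values enter a different analysis, where change is tested "between the initiation (D1) and the completion (M6) of the physical activity intervention using Wilcoxon signed-rank tests". They are also used in the McNemar comparisons of barriers and facilitators.

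The D1 data exist. Data Collection says: "All assessments are recorded at the baseline and the end of the 6-month physical activity program (M6) by the instructor". Table 1 ticks D1 and M6 for the activity questionnaire (IPAQ), quality of life and fatigue. Biological Data says: "A 7-mL blood sample is collected at the baseline (D1) and at the end of the study after 6 months (M6". Health status at entry is restricted by "Eastern Cooperative Oncology Group Performance status <2" (Study Population).

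The Abstract words the secondary objective as to "examine the effects of physical activity on physical, psychological, anthropometrics, clinical, and biological parameters".

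**The concern.** The trial has one arm, so how active a woman is was not assigned. The Intervention section also fits the programme and the step goal to her capacities and comorbidities, which ties activity to health by design. In metastatic disease a sicker woman is likely to walk less and also to report more fatigue and poorer quality of life. None of the three named covariates measures how ill she is.

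A regression on levels compares different women with each other and therefore picks up stable differences between them. The D1 values of activity and outcome are the most direct information on those differences that the trial holds, and they are not among the named confounders.

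At stake is how the secondary results are read. The objective speaks of effects of activity, and the Discussion expects the results to help design a multicentre randomised trial. An association that reflects only general health could influence which outcomes or biomarkers that trial pursues.

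**Working it through.** **Inputs from the document.** The recruitment target is 60 (Sample Size). The inputs there, 200 × 0.60 × 0.50, give 60 a year, or 60 × 9/12 = 45 in nine months, so n = 45 serves as a second case. Three covariates are named, taken here as one term each. The document gives no effect size, significance level or correlation for these regressions.

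**Assumptions.** Activity has no effect on the outcome. A shared health factor gives a same-visit correlation r between activity and outcome. Each variable has a D1–M6 correlation τ = 0.6. The health factor has a D1–M6 correlation ρ, where ρ = 1 means fully stable health. Tests are two-sided at 5%, and both levels are taken at M6.

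**Formulas.** Let c = rρ be the correlation of activity at one visit with the outcome at the other. The correlation each model tests is:

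- M6 levels only: r
- M6 levels plus D1 activity and D1 outcome: N/V, with V = 1 − [τ² + c² − 2rτc]/(1 − r²) and N = r − [2τc − r(τ² + c²)]/(1 − r²)
- change on change: r(1 − ρ)/(1 − τ)

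The rejection rate is about Φ(z − 1.96) + Φ(−z − 1.96), where z = atanh(correlation) × √(n − k − 3) and k is the number of other covariates. The direction of the regression does not matter: with one outcome, one activity measure and the same covariates, the t-test is the same whichever is the dependent variable.

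**Worked case: n = 60, r = 0.3, ρ = 1 (so c = 0.3).**

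- Levels, k = 3: z = 0.3095 × √54 = 2.27, rate 62%. With k = 0: z = 0.3095 × √57 = 2.34, rate 65%.
- D1 added, k = 5: V = 1 − (0.36 + 0.09 − 0.108)/0.91 = 0.624; N = 0.3 − (0.36 − 0.135)/0.91 = 0.053; N/V = 0.084; z = 0.61, rate 9%.
- Change on change: correlation 0, rate 5%.

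The same formula for levels gives 11% (k = 3) or 12% (k = 0) at r = 0.1, and 88% or 89% at r = 0.4.

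**Simulated false-positive rates, n = 60** (4000 runs per row for ρ = 1 in the first five rows, 3000 for the last three; the formulas agree within about two percentage points):

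| r | ρ | M6 levels only | D1 values added | Change on change |
|---|---|---|---|---|
| 0 | 1 | 5% | 4% | 5% |
| 0.1 | 1 | 11% | 5% | 4% |
| 0.2 | 1 | 33% | 7% | 5% |
| 0.3 | 1 | 62% | 9% | 5% |
| 0.4 | 1 | 88% | 15% | 4% |
| 0.3 | 0.8 | 64% | 30% | 22% |
| 0.3 | 0.6 | 63% | 61% | 64% |
| 0.3 | 0.4 | 63% | 90% | 95% |

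At n = 45, r = 0.3 and ρ = 1 the three rates are 49%, 8% and 5%.

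**Why the lower rows turn.** With r = 0.3, the correlation between the two changes is 0.3 × (1 − ρ)/0.4, which is 0, 0.15, 0.30 and 0.45 for ρ = 1, 0.8, 0.6 and 0.4. At ρ = 0.6 it equals the level correlation, and below that it exceeds it. Women who deteriorate lose both activity and well-being, and neither D1 adjustment nor differencing removes that.

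**The case against.** **The list is open.** A reader might infer that the plan rules out D1 values. It does not: the confounders are introduced by the word including, the article is a condensed text, and a full covariate list is often left to an analysis plan that is not shown. The time point of the level is also unstated, so the M6-on-M6 model above is a reading of the text. This part of the objection stands. What remains is that the article chose to name confounders and omitted the most informative ones it has, while the neighbouring analyses name D1 and M6 explicitly.

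**The analysis is exploratory.** Feasibility is primary, and change over time has its own tests. That lowers the stakes, but the label does not remove bias from an estimate.

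**The remedy can fail.** A reader might infer that change on change should replace the level regressions because it holds 5%. It does so only if health is constant. Sample Size expects 60% of patients to survive six months, so shifts in health over the study are plausible, and the last rows of the table show the advantage disappearing. This stands, and it is why change on change belongs in a sensitivity analysis.

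**Not every variable has two values.** The tracker is worn only during the intervention, so steps have no pre-intervention value. RECIST already describes progression over the period. Performance status appears only as an entry limit and is not listed in Table 1 or under Demographic and Clinical Data.

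**Smaller numbers.** A reader might take 60% of 60, that is 36 women, as the number analysed at M6. The 60% survival figure is already inside the 60, so that applies it twice.

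**Conclusion.** The point holds as an improvement to an exploratory analysis. The named confounders omit D1 activity and D1 outcome, both are collected for IPAQ activity and for the patient-reported and blood outcomes, and without them stable health differences can appear as an activity association.

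The size depends on correlations the document does not give. With fully stable health and n = 60, the levels-only rate runs from the nominal 5% at r = 0 to about 88% at r = 0.4, and D1 adjustment brings the upper end down to about 15%. At r = 0.3 the adjusted rate rises from 9% to about 30% if the health factor correlates 0.8 between visits, and there is essentially no gain at 0.6.

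It would go too far to say that a spurious association will appear. Entry is limited to performance status below 2, which narrows the range of health, and the strength of the shared factor is unknown.

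**What to change.** Amend the regression sentence in Statistical Methods so that it says the following:

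- The regressions use M6 values. For IPAQ activity and for outcomes measured at both visits, the D1 outcome and D1 activity are added to the named confounders, together with entry performance status where it was recorded.
- A regression of the D1-to-M6 change in outcome on the D1-to-M6 change in activity is given as a sensitivity analysis.
- Tracker steps (no D1 value) and RECIST (already a measure of change) are analysed separately and described as such.
- All results are reported as associations and not as effects of activity.

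The cost is two extra covariates per model, or three with performance status, and slightly wider intervals. No new data are needed. Confounding by progression between D1 and M6 remains and should be named as a limitation. The Results section says analyses began in February 2018, so a change made after that should be reported as such.

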Reportedly, regular physical activity and fatigue can affect blood biomarker levels, including inflammatory markers [26] and oxidative stress [27]. Evidence from randomized controlled trials (RCTs) has indicated an effect of physical activity in patients with cancer on the levels of circulating growth factors and cytokines (eg, interleukin 6 and tumor necrosis factor alpha) [28,29] and suggests that physical activity might markedly alter the frequency and functional competence of immune cell subsets of the innate immune system (eg, neutrophils, monocytes, and natural killer cells) [30,31]. Concerning the oxidative stress, an excessive accumulation of oxidative stress in cells has been shown to induce marked cellular and molecular damages and likely plays an important role in carcinogenesis, tumor promotion, and breast cancer recurrence and metastasis [32-34]. Moreover, plasma antioxidant defenses seem to be lower in women with breast cancer [34]. On the contrary, physical activity programs have shown to decrease the oxidative stress in patients with chronic diseases other than cancer, in particular through the improvement of enzymatic antioxidant defenses [27,35].

The Advanced stage Breast cancer and Lifestyle Exercise (ABLE) Trial was designed to address the gaps in the current literature. The primary aim is to determine the feasibility of an unsupervised and personalized physical activity intervention in patients with metastatic breast cancer. The secondary aims are to investigate (1) how the physical activity intervention changes the total global physical activity, sedentary time, and physical fitness; (2) how the physical activity intervention changes patient-reported outcomes, including the quality of life and fatigue; (3) how the physical activity intervention changes patients’ anthropometric measurements and body composition; (4) the barriers and facilitators of the adherence to a physical activity program; and (5) whether the physical activity intervention affects the oxidative stress and inflammation as biomarkers of the tumor progression.

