### Recruitment

Women are screened weekly during the center’s multidisciplinary metastatic breast cancer board meetings, as seen in Figure 1. After checking the inclusion and exclusion criteria, the study is directly proposed by an oncologist or radiotherapist to patients treated by chemotherapy or radiotherapy. As patients treated by hormonal therapy do not come to the center, they receive an information letter and study brochure through post and are contacted by telephone 1 week later to know whether they intend to participate. For all enrolled patients, a physician provides a certificate indicating no contraindications to physical activity, and an appointment is subsequently planned to sign an informed consent and proceed to the baseline evaluation (day one, D1).

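### As worded, the exploratory regressions make physical activity the response instead of the exposure, and adjust for an undefined visit count that may remove or create bias

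*Protocol article*

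**What the plan says.** The passage at issue is in Statistical Methods. After the Wilcoxon signed-rank tests of change from D1 to M6, it turns to "the level of physical activity according to biological, psychological, and clinical outcomes". The method for this part is given in the words "adjusted on potential confounders, including age, treatment, and number of visits, will be explored using multiple linear regressions". The section does not say what counts as a visit.

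The aims run from activity to outcome. The Objective in the Abstract reads: "Secondary objectives are to examine the effects of physical activity on physical, psychological, anthropometrics, clinical, and biological parameters". Aim 5 in the Introduction asks "whether the physical activity intervention affects the oxidative stress and inflammation as biomarkers of the tumor progression". One sentence in Principal Findings points the other way: the trial is also meant to "identify the determinants of physical activity".

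Contact is described in two places:
- Under Intervention (Adapted Physical Activity Program), "meetings at the center with physical activity instructors are proposed depending on" the needs of the patient, and "Patients receive feedback at least monthly from their instructor". Chemotherapy patients meet the instructor at day-care visits. Hormonal-therapy patients do so by phone or at a consultation.
- Recruitment explains postal contact with the words "As patients treated by hormonal therapy do not come to the center".

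**The concern.** There are two problems in one sentence.

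**Direction.** If activity is the response and fatigue, quality of life or a biomarker is a predictor, the coefficient is the difference in activity per unit of outcome. The objective asks for the difference in outcome per unit of activity.

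**Adjustment.** A confounder lies upstream of both exposure and outcome. Visits build up during the six months. If they include instructor meetings, they are partly the intervention itself, and they are offered by need. Need may depend on how active the patient is and on how ill she is. Conditioning on such a variable can open a non-causal path between activity and outcome.

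These models are the only covariate-adjusted link between activity and outcomes that the article names, and the Discussion says the results will help design a multicenter randomized trial. A coefficient that is hard to interpret could carry over into that design.

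**Working it through.** The document gives no figure for these regressions, so there is none to reproduce. The check compares passages and then uses illustrations whose coefficients are assumed.

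**1. Direction, side by side.** Statistical Methods: activity according to outcomes. Abstract Objective: effects of activity on outcomes. Aims 2, 3 and 5: how the intervention changes or affects outcomes. Taken literally, the first is the reverse of the second.

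**2. What the reversal changes.** With one outcome and the same covariates, both directions test the same partial correlation. One simulated data set with n = 60 (the planned sample) and three covariates gave t = 1.69 both ways, with coefficients 0.217 (outcome on activity) and 0.228 (activity on outcome). Their product should equal t²/(t² + df), with df = 60 − 5 = 55:
- 0.217 × 0.228 = 0.049
- 2.86/57.86 = 0.049

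So the p-value does not change, but the coefficient and its units do. If several outcomes enter one model for activity, the equivalence is lost, because each term is then adjusted for the other outcomes.

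**3. Where visits sit.** They accrue after D1. If they mean instructor meetings, they are intervention contact. If they mean hospital attendances, they follow the treatment schedule. Phone contact may not be counted at all, so similar contact could be recorded differently by treatment type.

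**4. Two structures compatible with the text.** Assumptions: T is binary treatment, noise terms are independent with variance 1 unless stated, and the true activity effect is 0.30.

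*A. Visits come first and affect both activity and outcome.* V = T + e; PA = 0.5V + e; Y = 0.3PA + 0.4V + 0.3T + e.
- Given T, Var(PA) = 0.25 + 1 = 1.25 and Cov(V, PA) = 0.5.
- Adjusting for T only: 0.30 + 0.4 × 0.5/1.25 = 0.46.
- Adding V: 0.30. Adjustment removes bias.

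*B. Visits respond to activity and to an unmeasured need U that also affects the outcome.* V = T − 0.5PA + 0.5U + noise (SD 0.7); Y = 0.3PA − 0.5U + 0.3T + e.
- Adjusting for T only: 0.30.
- Adding V: the slope of U on the part of V left after T and PA is 0.5/(0.25 + 0.49) = 0.676, so the activity coefficient is 0.30 − 0.5 × 0.676 × 0.5 = 0.13. Adjustment creates bias.

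Simulation with n = 400,000 agreed: 0.459 and 0.299 for A, 0.300 and 0.132 for B. The sign and size of the bias in B follow from the assumed coefficients.

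**5. The D1 value.** If an outcome's D1 and M6 values correlate at r, conditioning on D1 leaves a fraction 1 − r² of the M6 variance. For an assumed r of 0.5 this is 0.75, and for 0.7 it is 0.51. The gain for the activity coefficient is smaller where D1 status is itself related to activity, but in that case D1 status may confound and belongs in the model anyway.

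**The case against.** The strongest reply is that this is a single-arm trial, so the exposure in these regressions is achieved activity, itself a post-baseline variable. Being post-baseline therefore does not disqualify visits. They may precede the activity measure and affect both it and the outcome, as in structure A. This stands. A reader might infer that visits are definitely a mediator or collider; the documents do not support that, because they give neither the definition of a visit nor its ordering against the activity measure.

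A reader might also infer that treatment largely fixes the number of visits, so that collinearity damages the activity estimate. The article ties the place and mode of meetings to treatment, not their number. It sets a monthly minimum of feedback for everyone and makes meetings depend on need. It gives no figure for the overlap. Any inflation would fall mainly on the visit and treatment coefficients, not by itself on activity.

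On direction, the phrase is loose and the same sentence calls the other variables outcomes, so the intended model may already match the aims. Principal Findings gives some cover for modelling activity as the response. Both points are fair, but the listed aim closest to determinants concerns barriers and facilitators, which Statistical Methods analyses separately with McNemar tests.

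Finally, the list of confounders is introduced as non-exhaustive, and an article may leave the full model to a document not shown. So the absence of the D1 outcome value is not an error; adding it is an improvement.

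**Conclusion.** The point holds in limited form. As worded, the regression does not match the Abstract's secondary objective, and it treats as a confounder an undefined, post-baseline count that overlaps with treatment and possibly with intervention delivery. Whether adjusting for that count removes or creates bias cannot be settled from the document. The illustrations show that either can happen, with shifts of 0.16 (0.46 to 0.30) and 0.17 (0.30 to 0.13) on a true effect of 0.30. Those sizes rest wholly on assumed coefficients and are not estimates for this trial.

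Severity is minor to moderate. The analysis is exploratory. The feasibility proportion and the Wilcoxon tests of change do not depend on it. A reader might infer that the plan reverses all of its stated purposes or that its adjusted results will be invalid; the text supports neither.

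**What to change.** 1. For each outcome, make the M6 value the dependent variable and physical activity the exposure, and name the activity measure used. Take as covariates the D1 value of that outcome, age and treatment type at baseline.
2. Define number of visits: instructor meetings or hospital attendances, and whether phone contacts count.
3. Leave it out of the main model. Show a sensitivity analysis that includes it, and give the reasoning for each.
4. Report contact descriptively by treatment type.
5. If determinants of activity are also of interest, specify a separate model with activity as the response and label it as such.

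The cost is wording and one extra run per outcome. Table 1 already schedules the clinical and patient-reported measures and current treatment at D1 and M6, and Biological Data schedules blood at both times, so no new data are needed. The Results section says analysis began in February 2018, so the change should be dated and disclosed in the report.
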